### Equipment

An innovative Information and Communication Technology (ICT)-based virtual coaching system has been created to identify subtle changes in the physical, cognitive, psychological, and social domains of older adults. The e-VITA virtual coach is designed to offer personalized recommendations and interventions, fostering sustainable well-being within a smart living environment at home. All the devices will be supplied by the researchers.

The different components of the system are:

Coaches, consisting of social robots, that will interact with the users and are guided by apps;Sensors (both wearable and domestic) to detect physiological parameters, physical activities, and behavior of the users; these sensors are the Huawei smart band (wearable), the NeU device (wearable), and the DeltaDore system (domestic).Smartphones (the chatbot to provide insights, suggestion, and stimulation about healthy nutrition and physical exercise; the social platform to encourage users to share their interests).

These components (coaches, sensors, chatbot, and social platform) together with the main software named Digital Enabler (DE) constitute the Virtual Coach. The DE takes into account different types of data (both from the literature and different devices described above together with the user’s personal data), to make choices in order to customize the user experience. Choices are made both on the basis of the data received and the use case considered. The DE operates directly on the sensors, robots, and chatbots.

Categorizing sensing technologies and coaching devices based on their inputs is integral to establishing a cohesive and integrated sensor network. This network possesses the ability to recognize user behaviors, physiological states, and emotions, ultimately pinpointing a coaching device that resonates with the user’s preferences and acceptance.

Three categories of sensors could be distinguished: (1) those which are worn by the user and aim to sense physiological and actimetric parameters (user-related devices); (2) those which measure physical quantities useful for assessing the level of comfort and quality of the indoor environment and localization of the user (environmental devices); (3) those installed in the home to monitor user behavior and activities (home-based devices). For the e-VITA system, all these types of sensors are combined to make inferences about simple situations of the users (posture, activity level) in their environment and for localization in the home and the users’ physiological states. Contextual information is exploited by the interactive voice-based coaching system, the virtual coach. Each domain requires the integration of specific sensors to acquire heterogeneous data, and a coaching device is selected based on the user’s information, preferences, and technical characteristics and functionalities performed. This task is performed by the Use Cases Configurator, a tool that aims at identifying the optimal configuration of the sensor network and coaching devices to be used based on the user’s needs and requirements. The coaching devices can take four forms, namely, Gatebox, Nao, Google Nest Hub, and Celeste (or DarumaTO for Japan). The specific mobile applications for the usage scenarios are available on the Android smartphone, which is provided to the user as a support device.

### Technological description of coaches

The coaching devices used in the study are Nao Robot, Gatebox, and Celeste, substituted by DarumaTO for the Japanese centers (Table 1).

Nao is a humanoid Robot exhibiting a friendly appearance with eyes and movements reminiscent of a human being. Nao is equipped with an array of sensors, cameras, and microphones, enabling it to perceive and interact with its surrounding environment and human beings. It is powered by advanced artificial intelligence software, enabling capabilities, such as facial recognition, natural language understanding, and learning from user interactions (44–50).Gatebox is an intelligent home assistance device developed that appears as a holographic projector embedded in a cylindrical container, housing a virtual editable characteristic. This characteristic is a virtual assistant equipped with artificial intelligence, designed to interact with users akin to a personal assistant. From a technical standpoint, Gatebox utilizes holographic projection technologies to display coach characteristics within a three-dimensional environment. It is equipped with microphones and speakers to recognize and reproduce sound, allowing users to communicate with the virtual assistant through voice recognition and audio responses. Gatebox can perform a variety of tasks, such as providing information related to physical activity recommendations and giving dietary advice. Moreover, it is designed to provide a more intimate and personal interactive experience compared with other virtual assistants, incorporating elements of relationship and affection in its behavior (51–55).CelesTE (56–58) and DarumaTO (59–61) are social robots that have religion as a principal theme. CelesTE resembles an angelic statue atop a column inspired by sacred Christianity art and neoclassical architecture. This social robot incorporates the golden ratio to transcend its robotic nature and evoke a sense of holiness. Primarily designed as a “guardian angel” for older adults, CelesTE serves as a prayer companion and repository of religious teaching, including the Bible. AI enables short conversations on sensitive topics and can print selected content. DarumaTO is inspired by the traditional Buddhist and Shinto doll called Daruma. It can communicate through visual tracking and voice and facial expression. Its functionalities are similar to those of CelesTE, but in the case of design, it results in a device that has a familiar appearance to a Buddhist or Shinto older adults.

**Table 1 tab1:** Coaches.

Name	Type	Description	Main functionalities
NAO robot	Coaching device/Robot	Softbank NAO 5 and NAO 6 humanoid interactive mobile robot.	Robot platform that allows multimodal natural language interaction and robot autonomous movement.
Google Nest Hub (2e Generation)	Coaching device/Virtual assistant	Connected speaker enriched with a 7-chip touch screen	Screen whose brightness adapts to the room’s atmosphere. It has a loudspeaker and 3 microphones, making interaction possible.
Gatebox	Coaching device/Hologram	Hologram like device that projects characters with which the user can interact.	Internal sensors such as a camera and a microphone allow the user to converse with the projected character. It connects to the Internet via a wireless LAN. With infrared rays and Bluetooth, it can also be connected to household appliances and other devices.
CelesTE	Coaching device/Robot	Prayer companion designed for Christian Catholic users.	The intended main function of CelesTE is to be a “guardian angel,” especially thought for older people. It can be a prayer companion, and contains a vast number of teachings, including the whole Bible. Its AI is capable of keeping a short conversation, in which the user may ask and receive an answer about a sensitive topic (such as happiness, death, faith, etc.). It can also printout a selection of contents.

Such devices are in charge of interacting with the user, exploiting the dialog features provided by the platform.

The randomization technique, performed by the statistician, relies on a singular sequence of random assignments. A computer-generated list of random numbers is employed, and each subject is assigned a number based on their inclusion order in the study. Following this method, subjects are randomly allocated to the utilization of various coaching devices, maintaining an allocation ratio of five subjects for each branch.

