#### Sample size determination

In the study by Summers et al. (42), the EuroQol 5 dimensions (EQ 5D) was evaluated in two groups of older adults with physical pre-frailty conditions. EQ 5D, a test widely used to measure health status-related quality of life, was used to calculate the sample size. Assuming an overall sample size of 220 subjects (110 cases and 110 controls), 2 repeated assessments (baseline and follow-up), a significance level of 0.05, power of 90%, a correlation among repeated measures of 0.5, and a non-sphericity correction ε of 1 in an ANOVA model within-between interactions, the achieved effect size for this study is 11% (corresponding to a small effect size in a coherent way with the literature). Even factoring in a dropout rate of 10%, the total number needed would be 240 subjects, evenly divided into 120 cases and 120 controls. The hypothesis is that this sample size is more than adequate to detect variations in secondary outcomes. For these secondary outcomes, a treatment effect size is assumed to be similar to or even greater than the one identified for the primary outcome.

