**Figure 1 fig1:**
[figure not shown]
Flowchart of the patient selection.

In total, 120 subjects will be enrolled in the experimental group and will receive the e-VITA platform composed of a virtual coach, several sensors for monitoring, and a smartphone to use at home.

The control group will receive only the booklet with nutritional, cognitive, and physical suggestions.

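### Randomisation is described as one sequence with no country or centre restriction, and only for coaching devices, so balance by country is not secured; the device rules also disagree

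*Protocol article*

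**What the plan says.** **Method.** The randomisation paragraph follows Table 1, under Technological description of coaches: "The randomization technique, performed by the statistician, relies on a singular sequence of random assignments". A computer-generated list is used, and "each subject is assigned a number based on their inclusion order in the study". The paragraph names no block, country or centre.

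**What is allocated.** The same paragraph ends: "subjects are randomly allocated to the utilization of various coaching devices, maintaining an allocation ratio of five subjects for each branch". It does not define *branch*. It does not describe how a subject comes to be in the e-VITA arm or the booklet arm.

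**Arm sizes.** Sample size determination states that "the total number needed would be 240 subjects, evenly divided into 120 cases and 120 controls". The Intervention section, below Figure 1, agrees that "120 subjects will be enrolled in the experimental group".

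**Centres.** Study setting lists one institute each in Italy, Germany and France, and three in Japan. Participants gives 40 subjects per European country. The Discussion speaks of four sites.

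**Devices.** The Equipment section says: "The coaching devices can take four forms, namely, Gatebox, Nao, Google Nest Hub, and Celeste", with DarumaTO as the Japanese variant, and Table 1 also includes the Google Nest Hub. The text of Technological description of coaches says: "The coaching devices used in the study are Nao Robot, Gatebox, and Celeste", again with a Japanese substitute, and omits the Nest Hub. Equipment also says that the device is chosen on the user's "information, preferences, and technical characteristics and functionalities performed", a task given to the Use Cases Configurator. The section on that tool lists gender, age and religion among its inputs.

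**The concern.** A study-wide sequence by order of inclusion does not secure balance within a country. Country is a foreseeable prognostic factor here. It carries language and culture, one device exists only in Japan, and the Background section says that the project investigates how cultural aspects bear on acceptance of the technology and on the outcome. If one country's subjects fall unevenly between arms and country predicts change in EQ-5D-5L, the estimate becomes noisier. The repeated measures ANOVA in Data analysis names no country term.

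The paragraph describes the device draw but not the draw that defines the primary comparison. Its one numerical rule, five per branch, cannot be checked without knowing what a branch is. Two sections also give incompatible rules for how a participant receives a device, so centres following different sections would run the experimental arm differently.

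**Working it through.** **1. The plan's own figure.** Inputs from Sample size determination: N = 220, two assessments, correlation 0.5, alpha 0.05, effect size 0.11 (read as Cohen's f).
- Noncentrality = f² × N × m / (1 − ρ) = 0.0121 × 220 × 2 / 0.5 = 10.65, on 1 and 218 df.
- Power = 0.901. The stated 90% is reproduced.

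**2. Overall balance, assuming an unrestricted 1:1 sequence.** With X ~ Binomial(240, 0.5):
- P(X = 120) = 0.051.
- The central 95% range for one arm is 105 to 135.

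**3. Balance within a European country of 40.** With X ~ Binomial(40, 0.5):
- P(20:20) = 0.125.
- P(24:16 or worse) = 2 × P(X ≤ 16) = 0.268.
- P(at least one of three countries that uneven) = 1 − (1 − 0.268)³ = 0.608.

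This does not depend much on the sequence being unrestricted overall. Suppose the list is fixed at 120:120 but has no country strata (hypergeometric: 40 drawn from 240, of which 120 are experimental). Then P(20:20) in a given country of 40 is 0.137, and P(24:16 or worse) is 0.225.

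**4. What the imbalance costs.**
- Overall split of 105:135: relative information = 4 × 105 × 135 / 240² = 0.984. The noncentrality falls to 10.65 × 0.984 = 10.48 and power to 0.897.
- Split of 24:16 within one country, with country in the model: relative information from that country = 4 × 24 × 16 / 40² = 0.96, a loss of 4% there.

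**5. Five per branch.** Japan's share is 240 − 3 × 40 = 120. The article does not give enrolment per Japanese institute; an equal split would be 40 each. If *branch* means device within centre, the size of the experimental arm would be:

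| Centres | Devices | Total at five each |
|---|---|---|
| 6 | 4 | 120 |
| 6 | 3 | 90 |
| 4 | 4 | 80 |

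Only the first row equals the stated 120. If *branch* means device over the whole study, the total is 4 × 5 = 20 or 3 × 5 = 15. Under an unrestricted device draw with four devices, a centre with 20 experimental subjects would show exactly 5, 5, 5, 5 with probability 20! / (5!⁴ × 4²⁰) = 0.0107.

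**6. Device rule side by side.** Technological description of coaches has the device allocated at random. Equipment and the Use case configurator section have it selected from the user's characteristics and preferences. Table 1 describes CelesTE as intended for Catholic users, so the two rules would give different devices to real participants: one ignores religion, the other takes it as an input.

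**The case against.** The strongest reply is that this is a condensed article. Block sizes, strata and concealment often sit in the full protocol, and their absence is no finding. Random assignment to the two groups is stated elsewhere, and an unstratified list for 240 people is a legitimate choice. The clause about maintaining an allocation ratio implies some restriction, so the probabilities for an unrestricted draw may not describe the list actually used. All of this stands. It limits the point to what the paragraph does say: one sequence, study-wide order, no country or centre restriction, worded for devices.

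Several stronger readings are tempting and not supported:
- **That the method could never yield 120:120 or five per branch.** It can. It does not guarantee them, and the numbers fit exactly with four devices in six centres.
- **That control is one of five equal branches, with 240 / 5 = 48 people and a marked loss of power.** The text says five subjects per branch, not five branches, and both statements of arm size exclude it.
- **That the analysis ignores country.** Data analysis plans a regression of change adjusted for potential confounders. Country is not named, so adjustment is possible but not fixed.
- **That device comparisons are compromised.** No device comparison is planned, and device choice within the experimental arm leaves the e-VITA versus booklet contrast intact.
- **That chance imbalance biases the test.** Under random allocation it costs precision only. The analysis of change also removes much of any stable difference in level between countries.

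The three-versus-four mismatch may be editorial, since the three-device text itself points to Table 1. It still decides whether five per branch adds up.

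**Conclusion.** The point holds as a cheap improvement, not as a defect that threatens the primary comparison. As written, the method does not secure balance within countries of 40: 24:16 or worse has probability 27% per European country if the sequence is unrestricted, or 23% if it is balanced only overall. The consequence is country imbalance and a modest loss of precision, with overall power about 0.90 even at 105:135.

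The contradiction between random and preference-based device assignment, and between three and four devices, needs no assumption. The reading of five per branch as device within centre assumes six centres, with 40 in each Japanese institute if every centre is to hold 20 experimental subjects. The probabilities assume a 1:1 draw.

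**What to change.** - State the 1:1 allocation to e-VITA or booklet explicitly, in blocks, stratified by country and by institute in Japan.
- Define *branch*, and reconcile the number of devices and the number of sites across sections.
- Reconcile random with preference-based device assignment; the sponsor must state which applies. If random, use a separate list for device within the experimental arm. If preference-based, remove the statement of random device allocation and make no causal comparison between devices.
- Include country as a factor in the primary e-VITA versus booklet model.
- If allocation has already been done, report the list as it was used and adjust for country.

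As an illustration of feasibility, if there are four randomised devices and 40 subjects in each of six centres, blocks of eight (four control, one per device) give 40 / 8 = 5 blocks per centre. That yields 20:20 and five per device in every centre, and 120:120 overall. In that case one list could serve both purposes, though fixed blocks are easier to predict than varying ones.

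The cost is a revised list, a few sentences, managing six strata, and three degrees of freedom for country (five if institutes are fitted).

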### Technological description of sensors

The sensors are wearable and environmental, and they are needed to monitor physiological and environmental parameters. Table 2 presents the sensors available for the study.

**Table 2 tab2:** Sensors.

Name / Type	Description	Main functionalities	
DELTA DORE Tydom platform	IoT Device/Sensor	Set of sensors and measuring devices and IOT platform. The sensors can be used with a gateway connected to any dedicated platform.	Set of smart living sensors (motion sensors, door sensors, metering devices) and IOT platform.
Samsung Galaxy S20+ Smartphone	IoT Device	Android smartphone	To access all the apps and services
Smart band Huawei	IoT Device/Sensor	Wearable smart band that tracks physiological parameters.	Parameters monitored: activity level, step, calories, sleep duration, sleep quality, etc.
NEU XB-01	IoT Device/Sensor	Ultra-compact device with a butterfly-style design that bends in the middle to conform easily to any individual’s forehead. Data is transferred via Bluetooth in real-time to any smartphone, making it possible to measure brain activity.	Brain activity is measured using NIRS technology and the brain’s rate of blood flow change is measured using weak near-infrared light.

On the environmental sensors, Delta Dore motion detectors can detect the presence of a moving person in a room, which provides information on the occupancy of rooms and the movement of occupants from one room to another. This information can be of interest as a complement to the wearable sensors, especially when they are forgotten or under load. In this case, it is possible to use environmental sensors, especially motion sensors, to infer user activity. The sensor network, especially the infrared-based presence detection sensors (PIR sensors), should be strategically installed to effectively monitor the user, particularly in the designated areas of interest within the smart home environment. A predetermined selection ensures coverage of specific rooms. The primary objective of this system is to initially recognize the resident’s movements and potentially infer activities within a particular room of the apartment. The Use Case Configurator aggregates all the information detected by the environmental sensors, serving as input to feed the algorithms. Those sensors are:

The Wireless motion detector-Delta Dore DMB TYXAL. It is a motion sensor and not a presence detector. It has a range of 12 m with a 90⁰ opening angle. It generally covers one room, and detection is limited to opaque walls. Its autonomy is of the order of 10 years. The detector is based on passive infrared technology. The motion detection function consists of a pyroelectric sensor, the associated electronics, which process the signal and control the sensor power supply in an optimized way, and finally a lens.The Opening magnetic sensor–Delta Dore DO TYXAL+. DO TYXAL+ is an opening sensor developed to detect intrusion in dwelling when doors or windows are opened. It consists of two parts, one of which is attached to the door or window jamb, and this is the active element. The other part is a mechanical part that contains a magnet and is attached to the moving part of the door or window. These parts are attached to the doors with a double-sided tape. The sensor consists of a reed switch on the active element which is closed when the magnetic part is closed and opens when the magnet moves away from it, i.e., when the door is open. The technology is simple, robust, and energy-efficient.The Tydom Home. Sensors are battery-powered and communicate detection and maintenance information to a central unit. The Tydom Home IP gateway will be used to collect data from the various products and transfer them to the e-VITA configurator.

### Description of the end-users’ platform

The end-user’s platform is composed of a privacy dashboard, smartphone app, Chatbot, social platform, and use case configurator. Through those applications, the end-users will be capable of managing his/her data and receiving information on health activities and social events. However, the virtual coaches represent the main interface of the system through vocal communication with the end-users.

*Privacy Dashboard*: CaPe offers a privacy dashboard through the Cape Suite, compatible with any mobile device. This system is designed to adhere to legal requirements outlined in the GDPR. It incorporates consent-based data management, technical mechanisms for verifying compliance with data handling prescriptions, the right to obtain a copy of personal data, the right to be forgotten, and transparency tools on data usage. The consent record maintained by CaPe details who consented, when the consent was given, what was consented, how the consent was granted, and any instances of withdrawn consent. CaPe supports two types of consenting: (1) consenting to process within a service for a specific purpose and (2) consenting to share data from a service (source) to be processed in another service (sink) for a specific purpose. The Cape Suite features two frontend dashboards, catering to end-users (data subjects) and service providers (data controllers), respectively. The User Self-Service Dashboard serves as a centralized point for end-users to overview, verify, and modify data usage settings, understand the purpose of data processing, view event logs, and adjust linked services and consents previously granted. On the other hand, the Data Controller Dashboard is the entry point for service providers, allowing them to manage semantic descriptions and registrations of their provided services and view and manage service linking and consent status given by all users of their registered services. Some screenshots of the dashboard are shown in Figure 2.*Smartphone App and Chatbot*: The e-VITA project provides a smartphone app for end-users that functions as the control center. From there, users can access all relevant apps and interventions. Furthermore, apps that offer control over system settings, such as the privacy dashboard, can be reached via the control center. Specific e-VITA apps (e.g., social platform), but also external apps, are represented on the dashboard. The app requires a user profile to be accessed. After opening the app, users will observe an introduction to app which can be skipped to the landing page (see Figure 3A). From there, e-VITA users can create a profile using their email address and a secure password (see Figure 3B). Additional information is not needed for the sign-up process. The email and password will be used to log in and access the individual account (see Figure 3C).Further system control tasks, such as changing the language, password, or location, can also be handled via the smartphone app. The language settings can either be accessed via the landing page (see Figure 4A) or the general app settings (see Figure 4B). The general app settings are always accessible via a menu icon on the top left (see Figure 4C).The core function of the app is a control center through which various training interventions (e.g., cognitive training) and chatbots can be started. For this, the dashboard functions as a single point of contact (see Figure 5A). From there, other components of the e-VITA architecture can be accessed (see Figure 5B). The dashboard will provide links to, for instance, data analytics, profile data, performance indicators, status of the different interactive devices, privacy, and security.Users may want to use chatbots, social platforms, privacy dashboards, or other applications outside their home. To enable this, components of e-VITA that can be reached via URL can be accessed from outside the home, given that an internet connection is available. The dashboard consists of a grid layout with labeled tiles that link to other components of the e-VITA architecture. It is available in all languages of the e-VITA project. Users will observe this page after logging into their account. It offers a quick overview of all contents that can be accessed from the app.Chatbots are software agents that use a dialog function, such as a text or speech interface, and are based on natural language processing (NLP). The chatbot can be used to extract information from a user’s statement or input. The chatbot is also connected to the e-VITA dashboard. The chatbot in itself is a Telegram account that can automatically answer the text messages sent to it. To start a conversation with these chatbots, the user can either type ‘/start’ or press the start button on the screen. Once a piece of text is sent by the user to the chatbot, the message, the system starts to search for the intent and extracts entities from the user’s sentence. At the same time, the previous messages are also taken into consideration for extracting information that the user might have asked for before. Information is then returned to the middleware, where the request is further processed.*Social Platform*: The social platform allows the users to register and enroll in groups. Groups are meant to be interest areas. Users may either contact or create groups, based on their personal interests (e.g., nord walking and cooking classes), and may also get located to set up feeds, based on the country. Furthermore, users may be notified of upcoming meetings from groups and agenda updates of meetings. The main purpose is to establish a bridge between youth and older adults and between individuals and communities by creating a social platform in which different types of activities (e.g., cultural, sport, cooking, repairing, sewing, and gardening) are carried out to stimulate the users in remaining active. To make it efficient and easy to get connected, living labs, coaches, and those who offer their services will operate based on their location, which will be available only for the local community. Social platform application is maintained based on the countries and different communities (more specifically the local location and helping community directly around the primary end-users), to offer user services in the interest of the area. Living laboratories and international study site locations will be available to offer suitable activities to the users based on their location. For this purpose, in HumHub, Google location services will be used. Social platform operates as a website that can be accessed easily on any smartphone, tablet, and computer.Sign up: The application will ask to get permission of location to detect the user’s country to set up feeds based on the country. The user will enter credentials on the homepage, once registered.Registration: Upon registration, the user has designated roles such as administrator, service provider, or community organization (secondary stakeholders). Administrators are users who have technical responsibilities for the maintenance of the website, while service providers are users who offer either voluntary help or coaching. Community organizers are users who arrange local activities, such as meetups.Groups: There are different interest areas based on groups. Users may contact these groups or create groups based on their interests by themselves.Notification: In this section, the system will notify upcoming meetings from groups and agenda updates of meetings (update about the new updates of the app also). Notifications can be turned off in Settings.Messages: Users may contact people who initiate the activities or get contacted by the manager of those activities by getting detailed information through the chat system. When the users receive a message, they will be notified by message, such as email, and it will be marked on the top of the page. When a user clicks on the “Message” button, he/she will get a short description of the message, and in order to reply, users have to go to the “Conversation.”Feed: On feeds, users observe a variety of group meetings in the upcoming week. Moreover, they can review that volunteer announcements offer different services. The feed page is also considered as the main page, and users observe a review of the last activities.Settings: Users will be able to change location, language, and password and be able to log out. Furthermore, it is possible for the user to change or delete profiles on this page. Users can offer different types of services and, at the same time, benefit from offered services. Types of services will be offered under different categories. Users can also change their personal information on this page. This information includes profile photo, Email, and location. To make different changes to the profile directly, users have to click on their username, which is on the top of the page. The pop-up list will be shown, in which users choose “Settings” to make desired changes. On these settings, user can choose their desired language to use the application. To change the language, users have to choose “Settings,” and a core settings list will be shown, in which the “Language option” will be listed.
